## 9.8 Subgroup Analyses

The primary analysis will be repeated by age groups (0-<2 and 2-<4 months of age).

The primary analysis will be repeated by the presence of IS at the time of randomization (yes/no).

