## 4. Subject Selection

### 4.1 Number of Subjects and Sites

A total of 60 subjects will be enrolled in the clinical trial, i.e. 30 subjects per treatment group (see chapter 9.9).

The clinical trial will be multicenter study.

It is intended that the clinical trial will take place at approximately 17-20 sites.

To ensure the best possible distribution, the study has been announced on a German wide TSC meeting in February 2021. Subsequently, 16 German centres have declared their support in participating in the trial. To achieve the recruitment goal, the most promising centres were selected during pre-study visits. German-speaking centres in Austria and Switzerland were also included in the evaluation. All German TSC centres and associated clinics have announced their support in recruiting and / or referring patients to study centres.

If enrolment is delayed, additional sites may be recruited. Screening of subjects for this trial is competitive, i.e. screening for the trial will stop at all sites at the same time once a sufficient number of subjects has been included into the study. Investigators will be notified about screening completion and will then not be allowed to screen additional subjects. Subjects already in screening at this time will be allowed to continue to randomization if eligible.

If an insufficient number of study participants have been enrolled to meet the clinical endpoint, an extension of the enrolment period may occur.

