## 5. Treatment

### 5.1 Measures to minimize Bias

#### 5.1.1 Randomization

Within -14 days prior to study visit V1 and the time of randomization, all required elements of the screening visit will be fully completed and documented by a qualified staff member. For this purpose, informed consent must be obtained from legal guardian(s). The diagnosis of TSC must be confirmed based on the diagnostic criteria. Inclusion criteria and exclusion criteria must be reviewed and documented. Vital signs, physical examination results, EEG, abdominal sonography, and laboratory results must be complete. The results will be entered by a qualified member of the local study team with access to the eCRF. Subsequently, after internal validation, randomization is performed directly via the eCRF at the site on visit 1 and treatment will start at the same day after calculation of the starting dose. The randomization via the eCRF will trigger an email to inform the sponsor and the delegated persons by the sponsor. Eligible patients will be randomized 1:1 to interventional and control arm. Block randomization will be used to minimize the imbalance between the number of patients in each treatment group. While we are expecting no centre effects due to the highly standardized therapeutic management of TSC patients, age at inclusion might bias results. Since the primary endpoint is assessed at two years of age and age at inclusion might vary from 0 to <4 months, the total treatment duration will be different depending on the age at inclusion. Therefore, the randomization will not be stratified by centre but by age groups (0-<2 vs. 2-<4 months of age).

Blinding procedures for the groups are not applicable.

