### 9.4 Primary Analysis

As **primary analysis**, the BSID-III cognitive scale of 2 years will be analysed using a two-sided Mann-Whitney-U-test ( $\alpha=0.05$ ) stratified by age groups (0-<2 and 2-<4 months of age) comparing the treatment versus the control group. The Mann-Whitney-U-test is used instead of the t-test because there are hints that the values could be not normally distributed in this

|                                                                    |                                              |                                |
|--------------------------------------------------------------------|----------------------------------------------|--------------------------------|
| Clinical Trial Code: PROTECT
EU trial number: 2022-502332-39-00 | Trial Protocol
(Version 06; (01.10.2024)) | Page 92 of 110
CONFIDENTIAL |
|--------------------------------------------------------------------|----------------------------------------------|--------------------------------|

population. All patients randomized will be evaluated following the treatment policy strategy (ICH E9 R1).

Missing values of patients (including missing values due to early termination of the study) without a BSID-III cognitive scale at the age of 2 years will be replaced

- a) with randomly selected values of patients in the control group (single imputation) if the 1-year value is not available
- b) with data of the control patients using a linear regression model with the 1-year value as independent variable and the 2-year value as the dependent variable (single imputation) if the 1-year value is available

Values of the control group will be used in order to achieve a conservative estimate. No fixed value is used for single imputation (e.g. the median) to reduce the risk to underestimate the variance. The seed to select values randomly is 4421360.

Additionally, the median of the BSID-III cognitive scale and the corresponding 95% CI will be displayed by group.

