## 9.7 Sensitivity Analyses

The primary analysis will be repeated for the PPS as **sensitivity analysis**.

In addition, the primary analysis will be repeated using a linear mixed model with age groups and treatment as fixed factors and site as random factor. Missing values will be replaced using multiple imputation using age groups and the 1-year value as exploratory variables.

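### Section 9.8 repeats the primary test inside each subgroup, which asks whether there is an effect there and gives no estimate of whether the effect differs between subgroups

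*Protocol*

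**What the plan says.** Protocol section 9.8 has two sentences. The first reads "The primary analysis will be repeated by age groups (0-<2 and 2-<4 months of age", the second "The primary analysis will be repeated by the presence of IS at the time of randomization (yes/no". The analysis being repeated is in 9.4: the 24-month BSID-III cognitive score "will be analysed using a two-sided Mann-Whitney-U-test" at the 5% level, stratified by age group. Its only other stated output is that "the median of the BSID-III cognitive scale and the corresponding 95% CI will be displayed by group".

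The one model with age group and treatment together is the sensitivity analysis in 9.7, a "linear mixed model with age groups and treatment as fixed factors and site as random factor". Both enter as main effects. No treatment-by-subgroup term or between-subgroup contrast appears in the protocol, and it states neither expected subgroup sizes nor how differing subgroup results will be read.

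**The concern.** A subgroup analysis is meant to show whether the treatment effect depends on a characteristic, here age at start or IS at randomization. A test inside each subgroup has a different null hypothesis: no effect in this subgroup. Two such tests can differ because the subgroups are small or unequal, or by chance, while the effect is the same in both. The repeated analysis also gives no treatment difference with an interval, so a reader cannot compare effect sizes and is left with p-values and per-arm medians.

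At stake is how the supportive results are read. Section 1.1 counts IS among the most important risk factors for neuropsychologic impairment, and age at inclusion is the only stratification factor (5.1.1). A result that is significant in one subgroup and not in the other could be taken as evidence on which infants benefit.

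**Working it through.** **Inputs.** Section 4.1: "A total of 60 subjects will be enrolled in the clinical trial, i.e. 30 subjects per treatment group". Section 5.1.1: "Eligible patients will be randomized 1:1 to interventional and control arm", stratified by age group, so the arms are about balanced within each age group. Effects and SDs come from Table 8 and the text below it in 9.9; normal data, as assumed there. Subgroup splits are assumptions, because the protocol gives none.

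**Reproducing the plan's power.** With 30 per arm and the Mann-Whitney efficiency of 0.955 under normality, power ≈ Φ(δ / (SD·√(2/(0.955·30))) − 1.96). For 15 points and SD 15: 15/3.963 = 3.785, and Φ(1.825) = 96.6%. The other rows give 81.0% (15, SD 20), 62.2% (15, SD 25) and 82.7% (11.5, SD 15). Simulation gives 96.0%, 79.3%, 60.6% and 81.1%. Table 8 states >95%, >80%, >62% and >80%, so both methods agree with it within about 2 points or exceed its thresholds.

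**Disagreement under one common effect.** The subgroups are independent. With power pA and pB inside each,

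P(exactly one significant) = pA(1 − pB) + pB(1 − pA).

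The values of pA and pB come from simulating the exact two-sided Mann-Whitney test at 5% (40,000 runs each).

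| Effect, SD | 15+15 per arm | 20+10 | 24+6 | 27+3 |
|---|---|---|---|---|
| 15, 15 | 40% | 49% | 66% | 94% |
| 15, 20 | 50% | 54% | 62% | 74% |
| 15, 25 | 44% | 46% | 50% | 56% |
| 11.5, 15 | 50% | 55% | 63% | 77% |
| 11.5, 25 (text of 9.9 only) | 33% | 34% | 36% | 36% |

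Examples:
- First row, 15+15: pA = pB = 0.72, so 2 × 0.72 × 0.28 = 0.403. Both age groups are significant in 0.72² = 52%.
- First row, 20+10: 0.851 × 0.491 + 0.509 × 0.149 = 0.494.
- First row, 24+6: 0.908 × 0.700 + 0.300 × 0.092 = 0.663.

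With Table 8's inputs after missing values (simulated with a normal approximation) the 15+15 range is 41-49%.

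**The small IS group.** The columns 24+6 and 27+3 are read as IS no + IS yes. The smallest exact two-sided p with n against n is 2/C(2n, n): 2/20 = 0.10 for n = 3 and 2/70 = 0.029 for n = 4. At 3 against 3 the test cannot reach 0.05, so pB = 0 and disagreement equals pA. A normal approximation without continuity correction gives p = 0.0495 at full separation of 3 against 3, and so wrongly allows rejection. IS is not a stratification factor, so the arms may also be uneven. Keeping the age strata inside the IS group cannot lower the minimum p, because it only reduces the number of permutations.

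**Comparison.** A treatment-by-subgroup interaction test in a linear model signals a difference in 4.8-5.2% of the common-effect trials (splits 15+15, 20+10 and 25+5). For a true 15 points in one of two equal subgroups and 0 in the other, its power is 48% (SD 15), 30% (SD 20) and 21% (SD 25).

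**The case against.** The strongest objection is that the protocol never says subgroup p-values will be compared. Section 9.8 has no decision rule and makes no subgroup claim. Section 9.3 leaves detail and possible additional analyses to the SAP, and nothing excludes an interaction analysis there. Within-subgroup results are a normal part of reporting, and these do not touch the primary conclusion. This stands in part. The disagreement rates describe an inference that a reader may draw, not one the document makes. But 9.8 already names a method, and that method does not address effect differences, so the point is about what is stated and not about absent SAP detail.

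The gain from the fix is also limited. The interaction test has low power, and the linear model leans on approximate normality, which 9.4 doubts when it chooses a rank test. That stands too, and it is why the fix asks for an estimate with an interval.

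Three stronger readings are tempting and not supported:
- That an equally effective drug would usually look effective in one age group only. At 15+15 no Table 8 scenario exceeds about 50%, and with 15 points and SD 15 the most common result is both groups significant (52%).
- That it would almost always look effective only without IS. That specific pattern, pA(1 − pB), has a probability of about 44-64% with 6 per arm and 56-94% with 3 per arm, and the IS share is unknown.
- That timing within the first four months is a central question. No objective or endpoint in section 2 concerns it. Section 5.1.1 stratifies because treatment duration differs, and the period of opportunity described in 1.1 is the first year of life, which contains both strata.

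**Conclusion.** The point holds as an inexpensive improvement to a stated method. The only subgroup method fixed in 9.8 tests for an effect within each subgroup and provides neither a between-subgroup contrast nor a treatment difference with a CI. If the results are compared, one common effect gives discordant age results in about 40-50% of trials at 15+15 per arm and 46-55% at 20+10 in the Table 8 scenarios. With 11.5 points and SD 25 it is about 33%. For IS it is about 50-66% with 6 per arm and 56-94% with 3 per arm, where an exact test cannot succeed. An interaction test would mislead in about 5%.

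These figures rest on normal data, equal arms within subgroups, no missing values and assumed splits. They do not show that the sponsor intends to compare p-values, and the primary analysis is unaffected.

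**What to change.** In 9.8, or in the SAP:
- Add a treatment-by-age-group term to the linear mixed model of 9.7. In a separate model, add an IS main effect and a treatment-by-IS term. Report the interaction estimate with its 95% CI as the subgroup result.
- Show the treatment difference with 95% CI in each subgroup, model-based or Hodges-Lehmann, without declaring significance per subgroup.
- Report the IS-yes group descriptively if either arm has fewer than 4 children.
- Describe these analyses as exploratory.

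The cost is a few model terms and revised wording. No new data are needed and the primary analysis does not change, so the amendment rule in 9.3 for primary-analysis changes is not triggered. The downside is an interaction estimate with a wide interval at 60 children that depends on approximate normality.

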## 9.9 Sample Size/Power Calculation

It seems feasible that 60 patients can be randomized. To randomize 60 patients, 120 patients need to be assessed for eligibility assuming 50% willingness to participate in the trial. Assuming that 30 patients per group can be randomized, a difference of 15 in the cognitive scale of BSID-III at age 2 years will be detectable with a power of >95% using a two-sided Mann-Whitney-U-test ( $\alpha=0.05$  and under normality assumption with a standard deviation (SD) in each group of 15). We consider an improvement of 15 in the cognitive scale of BSID-III at the age of two years (e.g. a score of 75 in the control group and a score of 90 in the treatment group) relevant for reducing neuropsychological impairment, therefore lifting burden of disease and improving social participation and opportunities in school and professional life. The following Table 8 shows the resulting power for 30 patients per group under different assumptions:

Table 8: Power for 30 patients per group under different assumptions

| mean difference | SD per group | power | mean difference considering missing values | SD per group considering missing values | power considering missing values |
|-----------------|--------------|-------|--------------------------------------------|-----------------------------------------|----------------------------------|
| 15              | 15 (a)       | >95%  | ~ 13.5                                     | ~14.7/~15.5                             | >90%                             |
| 15              | 20           | >80%  | ~ 13.5                                     | ~19.7/~20.2                             | >70%                             |
| 15              | 25 (b)       | >62%  | ~ 13.5                                     | ~24.6/~25.1                             | >50%                             |
| 11.5            | 15 (a)       | >80%  | ~ 10.4                                     | ~14.7/~15.2                             | >70%                             |

a) [15, 99] b) [100]

If the improvement is only 11.5 and assuming a SD in each group of 15 (sample size of 30 per group), the power is still >80%. If the mean difference is 15 and the SD is 25 in each group, the power is reduced to >62%. If the improvement is 11.5 and the SD is 25 in each group, the probability to observe an improvement (difference in medians) >5 is still >75%. An observed improvement (point estimate) of 5 still seems encouraging to proceed, as in this range it can trigger

|                                                                    |                                              |                                |
|--------------------------------------------------------------------|----------------------------------------------|--------------------------------|
| Clinical Trial Code: PROTECT
EU trial number: 2022-502332-39-00 | Trial Protocol
(Version 06; (01.10.2024)) | Page 94 of 110
CONFIDENTIAL |
|--------------------------------------------------------------------|----------------------------------------------|--------------------------------|

an individual change from mild intellectual disability to learning disability with implications on social integration, education and professional perspectives.

A rate of missing values of 10% is assumed, in accordance with assumptions made by a comparable trial of mTOR inhibitors in children with TSC [42]. In addition, the EXIST-3 trial, enrolling 366 children and adults with TSC, reported a drop-out rate of 5% [23]. Therefore, a rate of missing values of 10% seems reasonable. The table above (Table 8) shows the reduction of the power, the reduction of the effect and the change of the standard deviation considering 10% missing values and the replacement method. The standard deviation in the control group was slightly reduced, in the treatment group slightly increased on average in the simulations.

Patients with missing values (including missing values due to early termination of the study) will not be excluded from the FAS and the SAF. Therefore, patients won't be replaced.

|                                                                    |                                              |                                |
|--------------------------------------------------------------------|----------------------------------------------|--------------------------------|
| Clinical Trial Code: PROTECT
EU trial number: 2022-502332-39-00 | Trial Protocol
(Version 06; (01.10.2024)) | Page 95 of 110
CONFIDENTIAL |
|--------------------------------------------------------------------|----------------------------------------------|--------------------------------|

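### Section 9.9 gives only the favourable chance of passing its 5-point mark, and two Table 8 powers are 1 to 2 points high for the Mann-Whitney test

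*Protocol*

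**What the plan says.** Protocol 9.9 bases its powers on 30 children per arm ("Assuming that 30 patients per group can be randomized"). The headline effect of 15 points is said to be "detectable with a power of >95% using a two-sided Mann-Whitney-U-test", "under normality assumption with a standard deviation (SD) in each group of 15". Table 8 then gives, without missing values, >95% (15/SD 15), >80% (15/SD 20), >62% (15/SD 25) and >80% (11.5/SD 15). The text repeats the third: "If the mean difference is 15 and the SD is 25 in each group, the power is reduced to >62" per cent.

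The combination 11.5/SD 25 has no row in Table 8 and no stated power. For it the text says instead that "the probability to observe an improvement (difference in medians) >5 is still >75" per cent, and continues: "An observed improvement (point estimate) of 5 still seems encouraging to proceed". The probability of passing 5 points when sirolimus has no effect is not given.

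Section 9.4 fixes a two-sided Mann-Whitney test stratified by age group as the primary analysis and adds that "the median of the BSID-III cognitive scale and the corresponding 95% CI will be displayed by group".

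**The concern.** A benchmark on an observed estimate can be judged only from both sides: how often it is passed when the drug works, and how often when it does not. Section 9.9 gives the first and omits the second. It does so in the scenario where the planned test is weakest, so the >75% stands where a much lower power would otherwise appear.

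The benchmark also uses the difference in sample medians, which is less precise under the protocol's own normal model than the shift estimate belonging to the Mann-Whitney test. A reader of a non-significant result with a 5-point difference could cite 9.9 as support for further exposure of young infants without knowing how often chance gives the same picture.

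The second, smaller issue is that two of the stated power bounds are not quite reached by the test they are attributed to.

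**Working it through.** **Inputs (protocol 9.9).** n = 30 per arm; normal scores with equal SD; two-sided α = 0.05; Mann-Whitney test; 5-point mark; effects 11.5 and 15; SDs 15, 20 and 25.

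**1. The plan's >75%.** For normal data the difference in medians has approximate SE = SD × √(π/2) × √(2/30). At SD 25 this is 25 × 1.2533 × 0.2582 = 8.09. With true effect 11.5, P(difference > 5) = Φ((11.5 − 5)/8.09) = Φ(0.803) = 78.9%. Simulation of 400,000 trials gives 79.5% (SE 7.9). The stated >75% is reproduced.

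**2. The same calculation with no effect.** P(difference > 5) = 1 − Φ(5/SE).

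| SD | SE (formula) | No effect, formula | No effect, simulated |
|---|---|---|---|
| 15 | 4.85 | 15.2% | 14.6% |
| 20 | 6.47 | 22.0% | 21.4% |
| 25 | 8.09 | 26.8% | 26.4% |

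Replacing 10% of values from controls leaves the SD 25 figure at 26.2%.

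**3. Power at 11.5/SD 25.** Simulated Mann-Whitney power is 39.3 to 39.9%. As a check, the normal approximation with the 3/π efficiency uses SE = SD × √(2/30) × √(π/3) = 25 × 0.2582 × 1.0233 = 6.605. Power = Φ(11.5/6.605 − 1.960) = Φ(−0.219) = 41%. So power is about 40%.

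**4. The matching estimator.** The Hodges-Lehmann shift has that same approximate SE, 6.6 (6.6 to 6.7 simulated), against 7.9 for the difference in medians at SD 25.
- No effect: 1 − Φ(5/6.605) = 1 − Φ(0.757) = 22.5% (simulated about 23%).
- Effect 11.5: Φ(6.5/6.605) = Φ(0.984) = 83.7% (simulated 83 to 84%).

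**5. Table 8 without missing values.** The simulated range runs from the test with continuity correction to the test without it.

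| Effect/SD | Stated | Mann-Whitney, simulated | 3/π approximation | t-test |
|---|---|---|---|---|
| 15/15 | >95% | 95.9–96.0% | 96.6% | 96.8% |
| 15/20 | >80% | 79.0–79.4% | 81.0% | 81.5% |
| 15/25 | >62% | 60.0–60.6% | 62.2% | 62.8% |
| 11.5/15 | >80% | 80.6–81.1% | 82.7% | 83.1% |

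The approximation for the two rows in question is Φ(15/(20 × 0.2642) − 1.960) = Φ(0.879) = 81.0% and Φ(15/(25 × 0.2642) − 1.960) = Φ(0.311) = 62.2%. Simulating the age-stratified test gives 79.1% and 60.2%. The first and fourth rows hold for the stated test. The second falls short by 80 − 79.4 = 0.6 to 80 − 79.0 = 1.0 points, the third by 62 − 60.6 = 1.4 to 62 − 60.0 = 2.0 points.

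The columns that allow for missing values also hold: 91.1%, 70.4%, 50.9% and 72.0% against >90%, >70%, >50% and >70%.

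**The case against.** Several objections carry weight, and four stronger readings should not be drawn.

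- **That 5 points is a go rule.** It is not. The sentence is a remark in the sample-size rationale, and no success criterion or continuation decision is attached to it. Sections 3.4 and 9.6 plan no interim analysis for efficacy or futility. The only inferential criterion is the test at 0.05. The 26% is therefore the chance of a misleadingly encouraging estimate, not the error rate of a procedure.
- **That >80% and >62% are t-test powers.** The t-test meets both bounds, but so does the 3/π approximation, a standard Mann-Whitney formula. The figures cannot show which was used.
- **That >75% is wrong once 10% of values are missing.** The protocol states it without reference to missing values, and it reproduces. A figure of 74.5 to 74.7% arises only if every missing child falls under imputation rule (a) in 9.4 with resampled control values. Fresh draws from the control distribution give 75.0 to 75.2%. Under rule (b), assuming a 1-year/2-year correlation of 0.5 to 0.7 and a 1-year effect of half to all of the 2-year effect, it is 75.6 to 78.7%.
- **That per-arm medians are the only planned effect display.** The linear mixed model in 9.7 has treatment as a fixed factor and so gives a between-arm estimate. Section 9.3 leaves further detail to the SAP.

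It is also fair to say that the Hodges-Lehmann shift lowers the no-effect probability only from about 26% to about 23%, that SD 25 is the least favourable SD considered, and that power gaps of 0.6 to 2.0 points change no decision when the sample size is set by feasibility. All of this stands and fixes the severity. None of it supplies the missing no-effect probability or brings the two bounds within reach of the stated test.

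**Conclusion.** The concern holds as a minor point. Section 9.9 presents one side of its 5-point mark. At the SD for which it quotes >75%, chance alone passes the mark in about one trial in four, and the primary test has about 40% power. At SD 15, the SD of the headline calculation, the chance figure is 14 to 15%. Two no-missing powers are about 1 and about 2 points high for the Mann-Whitney test: about 79% and about 60%.

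The figures assume 30 per arm and normal, continuous scores with equal SDs; apart from the stratified powers, they ignore the age strata. The protocol does not state the step size of the score. If scores were rounded to 5 points and bounded at 55 and 145 (an assumption), the no-effect share at SD 25 would be 21% strictly above 5 and 32% at 5 or more. At effect 11.5 the shares would be 74% and 84%. The conclusion does not depend on this.

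**What to change.** 1. In 9.4, report the age-stratified Hodges-Lehmann shift between arms with its 95% CI, beside the per-arm medians. In 9.9, base the 5-point remark on that estimate.
2. In 9.9, state beside the >75% the probability of passing 5 points with no effect (about 26% at SD 25 for the difference in medians, about 23% for the Hodges-Lehmann shift) and the Mann-Whitney power of about 40% at 11.5/SD 25.
3. In Table 8 and the text, restate the no-missing powers as about 79% (15/SD 20) and about 60% (15/SD 25).

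The cost is a few sentences in 9.4 and 9.9 and two slightly less favourable figures. The sample size, primary test, imputation and conduct of the trial are unchanged.
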